### Sample size calculation

2.3

For the sample size calculation, we made the following assumptions. First, the risk reduction applies to the entire intervention group, as the intervention consists of a single-cycle measurement and adjustment strategy, irrespective of whether this leads to a dose adjustment or DOAC switch. Second, the yearly incidence of the composite endpoint is assumed to be 15% to 20% in the control group, based on the literature [14], and 10% to 15% in the intervention group, based on an estimated absolute reduction of 5% after the single-cycle measurement and adjustment strategy. With a 1:1 allocation and a 2-sided α level of 0.05, 686 to 905 participants are required in each treatment arm to have a power of at least 0.80. Considering a drop-out percentage of ∼10%, a total of 1509 to 1991 participants is required and will be included.

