#### Randomization and blinding

2.4.2

After written informed consent has been given, the coordinating investigator will randomly assign the participant using Castor electronic data capture software. For in-hospital participants, the randomization will occur after a medically stable situation. As we would like to ensure a balance in sample size across the intervention and control groups, we will use block randomization. Randomization will additionally be stratified by center and by new vs “experienced” users. Blocks will be randomly chosen to determine the assignment of all participants.

Blinding of study participants is not feasible, nor is blinding for health care providers. However, blinding will be implemented for outcome assessors.

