#### Baseline data collection

2.4.3

In all patients, during the baseline visit, the following patient demographics and characteristics will be collected: medical history (Charlson Comorbidity Index [15]), weight, length, medication use, age, sex, frailty using the CFS [16,17], cognition using the Six-Item Cognitive Impairment Test [18], calf circumference, 4-m walk test and hand grip strength to screen for sarcopenia/low muscle mass, history of falling, Activities of Daily Living using the KATZ-score [19], Lawton Instrumental Activities of Daily Living score [20], living situation, CHA_2_DS_2_-VA (Congestive heart failure, Hypertension, Age, Diabetes, Stroke, Vascular disease, Age) and HAS-BLED (Hypertension, Abnormal renal/liver function, Stroke, Bleeding, Labile INR, Elderly, Drugs/alcohol) scores, and assessment of quality of life using the EQ-5D-5L questionnaire [21] (Supplementary Table 1). In addition, routine laboratory tests (creatinine and estimated glomerular filtration rate, hemoglobin and platelet counts, alanine transaminase and gamma-glutamyltransferase) will be performed. Information on bleeding and thrombosis history and medication adherence using the Medication Adherence Rating Scale 5 [22] will be collected.

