#### Follow-up visits

2.4.7

During the 2-year follow-up period of the study, participants will be contacted every 6 months by telephone (Figure 3).

During the telephone visit, the occurrence of bleeding or thrombosis will be evaluated and several questionnaires, as stated above, will be completed. Telephone visits are preferably conducted with the participant; alternatively, they may be conducted with a family member if necessary. For nursing home residents unable to complete questionnaires, a health care professional is contacted to assess, eg, occurrence of bleeding. In addition to these telephone visits, the EPR system will be consulted to identify/confirm the occurrence of complications and evaluate, eg, compliance.

Information on DOAC levels measured at the occurrence of a complication (bleeding/thrombosis) in the total research population will be collected through evaluation of the EPR. Nowadays, it is often standard care to perform a DOAC level measurement in such urgent medical situations in many academic hospitals.

In addition, evaluation of the EPR will be conducted to identify any (potentially) missing data and to gather information on changes in kidney function, medication, weight, and the standard care provided.

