### Data analysis

2.5

After the first 100 patients in the intervention group have completed the single-cycle measurement and adjustment strategy, an analysis will be conducted to determine whether a second DOAC measurement is necessary, provided that the first DOAC measurement falls within the expected therapeutic range.

Baseline characteristics will be presented stratified by allocation. The primary analysis will be performed according to the intention-to-treat principle. In addition, a per-protocol analysis will be conducted. To evaluate whether the single-cycle measurement and adjustment strategy is superior to standard care with respect to the composite endpoint, a competing risks survival model according to Fine and Gray will be used to analyze time to first event, accounting for competing events. The effect of treatment will be expressed as hazard ratios with corresponding 95% CIs. The proportional subdistribution hazards assumption will be assessed using appropriate diagnostic methods. Recurrent events and their nature will be summarized descriptively. Depending on the distribution of event counts, additional analyses using Poisson regression may be performed to formally test differences in the number of events between groups.

Furthermore, the aforementioned analyses will also be conducted separately for new users and long-term users. In addition, subgroup analyses in participants aged > 70, > 80, and > 90 years will be performed. Last, participants requiring a switch to VKA will be excluded to perform subgroup analyses to evaluate the effect in participants who use a DOAC.

Two-sided *P* values < .05 will be regarded as statistically significant. Missing data will be imputed depending on the extent of missing data and the likely mechanism. Results will be expressed as odds/hazard ratios including 95% CIs.

Descriptive statistics will be used to present the prevalence of deviant DOAC levels. Logistic and linear regression analyses will be performed to estimate associations between potential predictors of deviant DOAC levels and actual levels (linear model) and a deviance indicator (logistic model). Mixed-effects regression models for repeated measures will be used to assess the effect of the intervention on quality of life over the course of follow-up. Fixed effects will be time, study group, their interaction, and a set of potential confounding variables.

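### The quality-of-life mixed model does not name baseline EQ-5D-5L or the randomisation strata, and on two of its three possible readings it gives up precision that costs nothing to keep

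*Protocol article*

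**What the plan says.** All references are to the protocol article.

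- **Baseline data collection (2.4.3)** includes "assessment of quality of life using the EQ-5D-5L questionnaire" for all patients.
- **Follow-up visits (2.4.7)**: over two years "participants will be contacted every 6 months by telephone", and the questionnaires are repeated at those contacts. That gives four follow-up occasions, or five with baseline.
- **Data analysis (2.5)**: "Mixed-effects regression models for repeated measures will be used to assess the effect of the intervention on quality of life over the course of follow-up". The terms are then listed: "Fixed effects will be time, study group, their interaction, and a set of potential confounding variables".
- **Randomization and blinding (2.4.2)**: "Randomization will additionally be stratified by center and by new vs “experienced” users".

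The text does not say whether the baseline score is an outcome row, a member of the unnamed covariate set, or unused. It also does not say which coefficient or contrast is the treatment effect.

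**The concern.** Randomisation gives both arms the same expected baseline EQ-5D-5L. A model can use that in two ways: by holding the baseline mean equal across arms, or by adjusting follow-up scores for the baseline score. The listed terms state neither. Three readings remain:

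1. Baseline is an outcome row and the group term is free. The effect is then a difference in change from baseline, and a baseline gap known to be zero in expectation is estimated anyway.
2. Only follow-up scores are outcome rows, and the baseline score is not used.
3. Only follow-up scores are outcome rows, and the baseline score is one of the unnamed covariates.

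Only the third is efficient, and the text does not state it. The meaning of the interaction also changes. Under the first reading it carries the treatment effect. Under the other two it measures only how the effect differs between visits. At stake are the width of the confidence interval for a secondary outcome and clarity about which number will be reported as the effect.

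**Working it through.** **The plan's own figures.** The article gives no SD, correlation, target difference or power for quality of life, so there is no figure on this point to reproduce. The per-arm number used below comes from the primary endpoint: "686 to 905 participants are required in each treatment arm to have a power of at least 0.80". With pooled variance, two-sided 0.05 and power 0.80,

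n = [1.96·√(2p̄(1−p̄)) + 0.8416·√(p₁(1−p₁)+p₂(1−p₂))]² / (p₁−p₂)².

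- 15% vs 10%: (0.9167 + 0.3925)² / 0.0025 = 686 (stated: 686).
- 20% vs 15%: (1.0532 + 0.4513)² / 0.0025 = 905.4, so 906 when rounded up (stated: 905).

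The figures reproduce, and this point does not affect them.

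**Variance of the quality-of-life contrast at one visit.** Assume n per arm, a common variance σ², complete data, and a correlation r between baseline and that visit. The value of r is an assumption; the article gives none.

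- Free baseline, difference in change: V₁ = (2/n)·2σ²(1−r) = 4σ²(1−r)/n.
- Follow-up score only, no baseline: V₂ = 2σ²/n.
- Common baseline mean, or baseline as covariate: V₃ = 2σ²(1−r²)/n.

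Hence V₃/V₁ = (1−r²)/[2(1−r)] = (1+r)/2, and V₃/V₂ = 1−r².

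| Assumed r | V₁ (σ²/n) | V₂ (σ²/n) | V₃ (σ²/n) | V₃/V₁ | V₃/V₂ |
|---|---|---|---|---|---|
| 0.5 | 2.00 | 2.00 | 1.50 | 0.75 | 0.75 |
| 0.7 | 1.20 | 2.00 | 1.02 | 0.85 | 0.51 |
| 0.9 | 0.40 | 2.00 | 0.38 | 0.95 | 0.19 |

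Generalised least squares with five occasions and compound symmetry gives the same V₃/V₁ ratios. For the average over the four follow-up visits the ratios are 0.60, 0.76 and 0.92.

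**Standard errors, in SD units, with 686 per arm:**

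- r = 0.5: √(2.00/686) = 0.0540 against √(1.50/686) = 0.0468.
- r = 0.7: √(1.20/686) = 0.0418 against √(1.02/686) = 0.0386.
- r = 0.9: √(0.40/686) = 0.0241 against √(0.38/686) = 0.0235.

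The interval narrows by 1−√0.75 = 13%, 1−√0.85 = 8% and 1−√0.95 = 2.5%. Fewer than 686 per arm may be analysable for this outcome, but the ratios do not depend on n.

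**Effect of adjusting for other covariates.** This was simulated with 2,000 trials, 686 per arm, r = 0.6, and one baseline covariate correlated 0.4 with both scores. Variances are relative to the change contrast:

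| Analysis | Without covariate | With covariate |
|---|---|---|
| Change from baseline | 1.00 | 1.00 |
| Follow-up only | 1.30 | 1.07 |
| Baseline-adjusted | 0.81 | 0.78 |

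The formulas give 1.25 for follow-up only (2.00/1.60) and 0.80 for baseline-adjusted (1.28/1.60), so the simulation agrees up to Monte Carlo error. The extra covariate is neutral or helpful. It does not replace the baseline score: 1.07 with the covariate alone, against 0.81 with the baseline score alone.

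**The case against.** The strongest reply is that the article never says baseline is an outcome row. It speaks of quality of life during follow-up, and the baseline score could be in the unnamed covariate set, in which case almost nothing is lost. The coding of baseline and the covariate list are also details that an article may leave to an analysis plan not shown here.

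Much of this stands. A reader might infer that the plan definitely fits a free group effect at baseline; the text does not establish that, so the first set of ratios is conditional. The reply does not remove the point, however. The article chose to list the model's terms, and the list contains no baseline score and no strata. The covariates are labelled as confounders, and where the same section illustrates such adjustment, for the mortality model, the examples are age, sex and comorbidity. The efficient reading is possible but unstated.

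Two further inferences should be resisted.

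- **Adjusting for confounders wastes precision.** It does not, as the simulation shows. The word is merely inapt for a randomised comparison.
- **The model treats deaths as ignorably missing.** The article gives no death rate and no rule for scores after death. It says only that imputation will depend on how much is missing and the likely mechanism, and mortality is analysed separately. The documents do not support that charge.

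**Conclusion.** The point holds as an efficiency improvement to a stated model for a secondary outcome.

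- If baseline is an outcome row with a free group term, the constrained variance at one visit is 0.75, 0.85 or 0.95 of the planned one for an assumed r of 0.5, 0.7 or 0.9. The gain is modest and shrinks as r rises.
- If only follow-up scores are used and nothing else stands in for the baseline score, the corresponding ratios are 0.75, 0.51 and 0.19. Other prognostic covariates would recover part of that loss.
- If the baseline score is already a covariate, only the strata and the named contrast remain to be stated.

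These ratios rest on the assumed r, equal variances and complete data; the five-occasion check and the visit-averaged ratios also assume compound symmetry. A reader might infer that chance baseline imbalance biases the planned result. It does not: the estimate is unbiased under randomisation on every reading. The primary analysis and the sample size are untouched, and the plan sets no precision target for quality of life that could be missed.

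**What to change.** In section 2.5, or in the analysis plan if one exists:

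1. State one of two models. Either keep baseline EQ-5D-5L as a response with its mean constrained equal across arms (time plus group by post-baseline time, with no group term at baseline), or model the 6-monthly follow-up scores with baseline EQ-5D-5L as a covariate.
2. Add the randomisation strata, center and new versus experienced user, as covariates.
3. Define the treatment effect as the arm difference at each follow-up visit.
4. Call the remaining adjusters prespecified baseline prognostic covariates rather than confounders.

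The cost is a few sentences of model specification. The baseline score and the strata are already collected, so no new data or visits are needed, and the abstract reports the trial as ongoing, so the change can be made before outcome data are analysed.

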### Patient involvement

2.6

A patient representative, who is also a member of the Client Council Thrombosis Services in the Netherlands, is part of the DOAC-FRAIL study team. He played an important role in the conceptualization of the study protocol and will be involved during the duration of the study.

### Ethics

2.7

The DOAC-FRAIL RCT will be conducted according to the principles of the Declaration of Helsinki (last revision, October 2024) and in accordance with the Dutch Medical Research Involving Human Participants Act law (WMO). The study protocol was approved by the Medical Research Ethics Committee (MREC) of MUMC+ (reviewing committee) and by the Central Committee on Research Involving Human Subjects (CCMO), the competent authority in the Netherlands (registration number EU CT-2025-521362-10-00). A Data Safety Monitoring Board has been established to oversee the study.

## Discussion

3

The DOAC-FRAIL RCT will be the first study to evaluate the efficacy of a single-cycle measurement and adjustment strategy based on DOAC peak plasma levels in reducing the number of adverse events among frail older patients, including nursing home residents. In addition, the DOAC-FRAIL RCT will yield substantive, currently missing, data on the overall efficacy and safety, including tolerance and adherence of DOAC use in the frail older population.

Frail older patients have been underrepresented in the pivotal landmark trials of DOACs [[1], [2], [3], [4]]. Nevertheless, the evidence derived from these trials is commonly extrapolated to clinical practice in this population. Emerging data, however, suggest that DOACs should be prescribed with greater caution in frail older patients, highlighting the need for further research. For example, the FRAIL-AF study demonstrated that actively switching frail older patients from VKAs to DOACs was associated with an increased risk of bleeding (odds ratio, 1.69; 95% CI, 1.23-2.32) without an increase in thromboembolic events [5]. In addition, several studies have shown that DOAC levels in frail older patients are often outside the expected on-therapy range, both in acute and stable medical conditions [6,[8], [9], [10]]. The clinical consequence might be the occurrence of more than predicted numbers of adverse events, including thromboembolic events or bleedings, based on the repeatedly reported risk associations between high DOAC levels and bleedings and low DOAC levels and thromboembolisms [[11], [12], [13]]. The DOAC-FRAIL RCT will determine whether a single-cycle measurement and adjustment strategy may contribute to a further reduction of adverse events in the frail older population.

Important features of the DOAC-FRAIL RCT include the use of DOAC peak plasma levels in daily practice, the inclusion of DOAC-naïve as well as DOAC-experienced patients, and specific representation of frail (CFS >3) older (≥ 70 years) patients, including nursing home residents. An innovative element is that the study protocol provides guidance on the interpretation and management, based on deviant DOAC levels for each specific DOAC and dose. This way, for the first time, we implement this laboratory biomarker in the management of anticoagulant treatment in complex patients. Moreover, it is the first study to implement laboratory guidance through DOAC monitoring in any patient population.

A limitation of correlating DOAC-plasma levels with outcomes is that measured plasma levels reflect only a single time point and may not represent overall exposure or the balance between thrombotic and bleeding risk. In addition, DOAC-plasma levels are influenced by factors including renal function, comorbidities, medication use, adherence, sampling time, and illness, and the absence of therapeutic ranges complicates interpretation. Moreover, clinical outcomes are often multifactorial in origin. Nevertheless, frail older adults more often have DOAC-plasma levels outside expected ranges, which are shown to be independently associated with bleeding and thrombotic events. Maintaining DOAC-plasma levels within expected ranges may therefore help to reduce complications and support individualized anticoagulant therapy.

If our hypothesis is supported by the study outcomes, our single-cycle measurement and adjustment strategy will contribute to a reduction in bleedings (including CRNM bleedings) and/or thromboembolism in the frail older population. This would be a breakthrough in DOAC management in this population. In addition, it may improve safe switching from VKA to DOAC, in those that qualify for DOAC management, specifically in the frail older population. If the study hypothesis is refuted, the obtained study data will be helpful in further refining anticoagulant management, as it provides a basis for exploring additional risk factors in frail older adults, an understudied population.

## Conclusion

4

This will be the first study to evaluate the efficacy of a single-cycle measurement and adjustment strategy for DOACs in frail older patients, including nursing home residents, in reducing adverse events, defined as major bleedings, CRNM bleedings, and thrombosis.
